### **6.7. Long-term follow-up assessments**

At baseline, we will request consent for linkage to routinely collected primary and secondary care health outcomes, which was acceptable in the Feasibility Study. Linkage will not occur during the lifetime of this study. The linkage will be to obesity related health conditions documented in GP and hospital records, hospital admissions, GP practice consultations and outpatient attendances, prescribing data.

### **6.8. Withdrawal criteria**

Participants will have a right to withdraw from the study at any time, without providing a reason. They may wish to withdraw from one or more aspects of the study (for example receiving the text messages, attending for weigh-ins, completing questionnaires, all contact from the study team, collection of routine data etc).

Participants will be informed that they can withdraw from any aspect of the study. Participants who stop the text messages can still remain in the study for follow-up. Any reason offered for their withdrawal will be documented on the CRF and a change of status form completed. Participants who withdraw will not be replaced as a 25% loss to follow-up has been accounted for in the sample size calculation. Participants who wish to withdraw from study follow-up should be asked to confirm whether they would

still be willing to consent to allow routine follow-up data to be used for trial purposes (hospital/GP medical records).

## **6.9. End of trial**

The end of follow-up for each participant is defined as the final data capture on that individual. The end of follow-up within the trial is defined as when the final data capture on the last participant occurs. The end of the trial is defined as the end of funding. The end of the trial will be reported to the Sponsor and REC within 90 days, or 15 days if the trial is terminated prematurely. If terminated prematurely, the Investigators will inform participants and ensure that the appropriate follow up is arranged for all involved, if appropriate. A summary report of the trial will be provided to the Sponsor and REC within one year of the end of the trial. An end of trial report is also issued to the funders at the end of funding.

## 7. TRIAL TREATMENTS

### 7.1. All groups - information resource and pedometers

At baseline all men (intervention and control groups) will be provided with a website containing a menu of evidence-based information resources including standard NHS information on weight loss (printed information will be provided to those without internet access), other support websites for men (MHF,) and a low cost pedometer. Pedometers encourage self-monitoring and increase physical activity, however alone they do not result in weight loss [11]. In our Feasibility Study, a low-cost pedometer was acceptable, including with men with reduced mobility and substantial co-morbidities. It was given to counter group allocation disappointment and address inequalities: in DE compared to AB socio-economic group households 6% v 24% of adults have access to wearable technology [28].

### 7.2. Control group

Waiting list for 12 months followed by 3 months of SMS (months 13-15 inclusive). At baseline, all groups will receive information (web page; written option) about weight loss and be given a pedometer. There are no interim measurements (at 3 and 6M). Men can choose whether to try to lose weight or not during the 12 months. The control arm is as close as possible to “doing nothing”, whilst remaining ethical by providing information, free choice to lose weight and later assistance via SMS to reduce disappointment bias. This control group design was decided through PPI consultation and qualitative research in the Feasibility Study and was acceptable to most men (only one man withdrew due to allocation disappointment). Men are assessed for the same outcome measures as the other groups at 12M and 24M only. No weight loss targets are set and men do not have access to a self-monitoring page.

### 7.3. Interventions

The interventions are described following the Template for Intervention Description and Replication (TIDieR) guidance [38]. They apply the principles of self-management, are designed to be efficient, and minimise burden on NHS weight management service staffing resources.

#### 7.3.1 SMS

**Why-theory:** The SMS were designed in collaboration with nine men from the University of Stirling Public Engagement Group and Men’s Health Forum and informed by: evidence based Behavioural Change Techniques (BCTs); systematic review of effective SMS studies [12] and analysis of qualitative data on acceptability and men’s preferences in the Feasibility Study. They were written with input from the editorial and creative consultant of Men’s Health Forum GB who has provided award-winning health guides and online material for men on weight and other health issues [26, 39]. SMS for 12M are

embedded with: evidence and theory-based BCTs based on the Health Action Process Approach [40], Self-Determination Theory [41] and the Behaviour Change Maintenance Model [42]. Daily SMS target automatic processes by acting as a consistent prompt and cue reminding participants of their intention to lose weight, thus aiming to reduce impulsive behaviours [43]. The following feedback from men in the target population was incorporated: include concrete tips, facts and links to information websites; include a range of perspectives and approaches as no one approach will suit everyone all the time; introduce engagement elements such as questions and prompting reflections. Men liked texts to seem as if they were coming from other men taking part in Game of Stones (*"like getting texts from your mates"*)

**Why-intervention components:** The SMS include BCTs which target motivation, self-regulation and maintenance processes, underpinned by a person centred-approach [44]. Some texts are derived from qualitative interview data from the Feasibility Study where men have told us what they find helpful. Engagement is encouraged by asking direct and rhetorical questions on weight management and employing general communication techniques such as agenda setting or use of humour. This is supported by qualitative data from our Feasibility Study and a qualitative evidence synthesis on obesity in men [45]. Men like factual information and banter, and dislike strict diets and being told what to do. Texts contain facts about losing weight: eating less, reducing portion size, healthy snacks, sugar and alcohol, sticking to a plan and increasing physical activity and exercise. Texts embed links to relevant websites for more information and self-monitoring sites (e.g. weight, step count). Information resources include: e.g. NHS choices, the Eatwell Guide; Man v Fat; Men's Health Forum. How participants act will depend on personal food preferences; gradual and achievable changes to their normal diet and activity will be suggested in line with recommendations [2]. The sequencing of SMS covers weight loss (until 6M), followed by more weight loss maintenance topics (months 6-12). Individual SMS are non-consecutive and stand-alone: they do not require paying attention to, or engaging with previous content. After each weight assessment at 3, 6 and 12M, men receive a personalised SMS including the participant's name and weight change.

**What-materials:** In addition to the SMS, participants are provided with a web-page (written information if no internet access) offering a choice of evidence-based weight management and physical activity approaches plus a pedometer to operationalise the self-monitoring BCTs in SMS.

**What-procedures:** Single SMS are sent at a default rate of 1 message per day between 9:00AM and 8:30PM, with options to reduce the number, based on Feasibility Study findings.

**Who provides:** The SMS intervention is delivered by the Health Informatics Centre (HIC) at the University of Dundee via tried and tested technology used in the Feasibility Study and other RCTs [31-33]. The intervention package is designed so that the SMS library can be readily delivered by other SMS providers to facilitate future roll out by the NHS or public services. To address our objective: to refine

the digital programming for future scalability and implementation, CHaRT will investigate further integration planning for Phase 3 of Game of Stones. Collaborators at the Digital Health Institute (DHI) who are funded by Scottish Government to progress digital innovation within the NHS will provide access to their sandbox early 2021. A sandbox is a piece of software that can access only certain resources, programs, and files within a computer system. CHaRT will explore the digital capabilities and infrastructure that is currently available to ensure that the delivery systems are future proofed as far as they can be for future implementation.

**How (mode of delivery):** Remote delivery. SMS are sent by the HIC automated system.

**Where:** SMS can be received anywhere depending on access and read at any time. Men require a mobile phone (any type, not just a smart phone) to maximise reach.

**When and how much:** Daily texts arrive at varying times between 9am and 8.30pm (preference for am or pm can be accommodated e.g. for men who work night shifts). Men can reduce the SMS frequency from 1 per day to 3 or 5 per week or increase it again to 7 per week (maximum). SMS can be stopped and restarted by a simple instruction e.g. "STOP TEXTS" and "RESTART". Men can stop the SMS but remain in the trial for assessments and follow up if they wish.

### 7.3.2 Intervention 2: endowment incentive adjunct to SMS

**Why-theory:** The novel endowment incentive for verified weight loss in addition to the SMS is based on theory [46, 47] and evidence [13-15, 48-50]. In the Feasibility Study, the incentive structure was decided by considering evidence from multiple sources: a Discrete Choice Experiment (DCE) completed by 1045 men in the target population; extensive PPI; systematic review evidence; psychological and economic theory and analysis of qualitative interview data [2]. The incentive draws on behavioural economics [46, 47] which shows that people ascribe more value to something because it belongs to them (endowment effect) and are more motivated to avoid losses than they are to achieve similarly sized gains (loss aversion).

**Why-intervention components:** The incentives are offered alongside the SMS because systematic reviews consistently report that financial incentives alone are unlikely to be effective for sustained complex behaviour change, without additional behaviour change strategies [14, 48, 51].

**What-materials:** All participants are 'endowed' with the financial incentive at the start of the trial. Money can only be accessed at 12M (no withdrawals) if weight loss targets are met. It is placed into a hypothetical personal account (held by the incentive provider) and a mock-up cheque, printed on high quality paper, is given to men at the start to encourage participants to feel ownership of the money.

**What-procedures:** Men receive the full incentive at 12M if they achieve all 3 weight loss targets, but they 'lose' money if targets are not met. Detail is described elsewhere [2]. The top level weight loss

target suggested by NICE is 10% [9] and this was endorsed by PPI. This is more ambitious than the 3% mean weight loss in weight management programmes quoted in NICE, current systematic review evidence for men with obesity [11] and the 5% weight loss at 12M in the FFIT trial [16]. The full incentive can be secured by meeting all verified weight loss targets: 5% of body weight lost (from baseline) at 3M, 10% lost at 6M and 10% lost at 12M. At 6 and 12M, some money for each % weight loss not attained between 5-10% is lost. Weight must be objectively measured by a Fieldworker (see Section 6.2 for Covid-19 procedures) within 3 weeks of the target date. The incentive is calculated automatically when verified weight is entered into the centralised database. Men then receive a personalised SMS with the amount of incentive secured/lost, are encouraged to keep trying as they can still secure money and this is also presented on their personal private SMS+I webpage.

All men are given a wallet-sized Game of Stones appointment card with their personalised target weights for each appointment date and Fieldworkers fill in objectively measured weight at each assessment.

**Who provides:** Incentives are provided as part of this NIHR research grant and are triggered by achieving target weight loss, verified by the Fieldworker. Feedback on weight achievement and incentive status will be through SMS and a study webpage.

**How (mode of delivery):** Men receive an automatic bank transfer of money to their bank account (BACS) once the automated database confirms the amount at the 12-month assessment. In the Feasibility Study, all participants had a bank account, however secure postal payment methods will be available if required.

**Where:** Weight goal verification is undertaken by Fieldworkers at places convenient for men, usually a health or community centre (See Section 6.2 for Covid-19 procedures). Entering participant weight onto the database triggers an automatic SMS notification.

**When:** At 12M men receive the money depending on weight loss achievements [2]. If weight at 12M exceeds baseline weight, no payment is given, regardless of whether interim weight loss targets were met, as recommended by participants in the Feasibility Study and PPI.

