**v) Informing the participant of group allocation:** After randomisation, usually at the baseline assessment appointment, the Fieldworker will inform the participant which trial group they are allocated to and ensure that they understand what will happen next. An additional specific post-randomisation PIL will be provided for each of the three intervention groups (Trial arm 1 PIL (SMS+I) together with a mock-up cheque for the incentive (see Section 7.3 for incentive detail), Trial arm 2 PIL (SMS only) and Trial arm 3 PIL (wait list) and discussed in detail with the participant. Once group allocation is known, a Fieldworker will talk through the relevant post-randomisation PIL, then complete documentation of weight target and assessment dates (on a wallet-sized Game of Stones appointment card given to the men). All men will be given a pedometer, shown how it works, and a unique login and password provided by CHaRT which will allow them to access the study website pages, appropriate for their allocated group. The Fieldworker will discuss the information and the personal web page which will show the targets, assessment dates, incentives (for SMS+I group) and the self-monitoring page. A PPI suggestion is for men to be able to upload selfie/photo to their personal password protected self-monitoring web page throughout the study, as image was considered a motivator for some men. This will be incorporated into the website re-design and will be optional, for self-monitoring and motivating purposes only. If the participant does not have access to a camera, the Fieldworker will offer to do this on the participant's behalf, using a secure Game of Stones tablet. They will delete the photo as soon as it is uploaded to the website. If the assessment is taking place remotely via video, a screen shot will be taken for men's personal web pages. The participant will have an opportunity to access the website with the Fieldworker present and ask questions to ensure that there are no operational problems. If there is no internet access, printed screenshots of the website will be available. Information about how the website works will be made available in a range of formats/media and will include Frequently Asked Questions.

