### **6.4. Blinding**

Primary outcome assessment will be blinded to group allocation and undertaken by a Fieldworker who has not previously met the man and/or is not aware of study group. This was tested in our Feasibility Study and found to be acceptable, understandable to participants and feasible logistically for Fieldworkers to implement. When assessments are arranged, participants will be asked not to inform the Fieldworker conducting follow-up appointments of their group allocation. Recruiting GP practices or other stakeholders who facilitate recruitment (e.g. community centre staff) will not be informed of group allocation. The statistical team analysing data will be blinded to group allocation and will not have access to data collected at 3M and 6M outcome assessments in the intervention groups during the primary analysis.

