Self-report questionnaires (participant choice, online, paper, telephone if visual impairment or literacy issues - method documented), completed when attending weight assessments, will be uploaded to CTU databases. The questionnaires are completed by the men with the researcher present in case they require help e.g. visual or literacy issues. When completed, the researcher will check to make sure there

is no accidental missing data (e.g. two pages turned over). If missing data is noticed after the assessment appointment, the participant will be phoned as soon as possible and given an opportunity to provide the missing data. Any missing data completed after the assessment will be logged. Assessments use validated tools where available and follow quality standards for measurement procedures.

To maximise completeness of data, participants who do not attend assessments within the 3-week time window permitted, but who have not withdrawn from the trial, may be contacted (by their preferred method) and requested to complete a questionnaire (preferred method) and provide a self-report weight. This will not qualify for an incentive payment. A letter will be sent to those who don't attend the 12M assessment reminding them that they will be invited to attend an appointment at 24M.

All participants receive a £20 voucher (Amazon or High Street) reimbursement of expenses for attending the 12 and 24M assessments, consistent with evidence that financial reimbursement can improve retention [36, 37]. In the Feasibility Study data quality was high, with low levels of missing data. The completion rates for self-reported secondary outcomes were 88-99%. The Delegation of Responsibilities Log will identify all trial personnel responsible for data collection, entry, handling and managing the database.

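### A 12-month assessor who completes the appointment card as Section 7.3.2 directs learns the man's allocation, and the stated blinding safeguards do not cover the card

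*Protocol*

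**What the plan says.** - **Blinding.** Protocol Section 6.4: "Primary outcome assessment will be blinded to group allocation". The assessor is to be someone new to the man and/or unaware of his group. Men are asked not to reveal it, and Section 6.1 (item vi) repeats this request for the 12-month visit.
- **Card.** Section 7.3.2: "All men are given a wallet-sized Game of Stones appointment card", that is, a "card with their personalised target weights for each appointment date and Fieldworkers fill in objectively measured weight at each assessment". Section 6.1 (item v) has the Fieldworker, once allocation is known, "complete documentation of weight target and assessment dates (on a wallet-sized Game of Stones appointment card given to the men".
- **Control arm.** Section 7.2 gives control men no interim measurements and assesses them at 12 and 24 months only. It adds: "No weight loss targets are set and men do not have access to a self-monitoring page".
- **Different schedules.** Section 9.3 confirms that 3- and 6-month assessments occur in the intervention groups only. It treats this as a blinding problem for the statistician, from whom those data are withheld.
- **Weighing.** Section 6.6 specifies calibrated scales, standardised procedures, one request on clothing and pockets for all men, and a participant signature agreeing the weight. On questionnaires it says: "The questionnaires are completed by the men with the researcher present in case they require help".

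**The concern.** The card is a physical record of a visit schedule that differs by arm, and the protocol tells the Fieldworker to write on it. At 12 months the person told to write on it is also the person who must not know the allocation. The protocol already accepts that interim weights reveal allocation, since it keeps them from the statistician. Nothing keeps the same information from the assessor.

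Blinded assessment of the primary outcome is a stated design property (Sections 5 and 6.4). Both primary comparisons are of an intervention arm with control (Section 9.3.2), which is the distinction that interim entries disclose. In the incentive arm the 12-month weight also bears on payment (Section 7.3.2).

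**Working it through.** No figure in the protocol bears on this point, so the check sets the instructions side by side.

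1. **Who writes on the card at 12 months?** Section 7.3.2 says Fieldworkers do so at each assessment. The 12-month visit is an assessment and is not excepted there or anywhere else.
2. **What is on the card by then?** Section 6.1 (item v) puts assessment dates and a weight target on it after randomisation. Section 7.3.2 adds each measured weight. An intervention man who attended his interim visits has 3- and 6-month weights on it. Sections 7.2 and 9.3 rule these out for a control.
3. **Does the result depend on who holds a card?** The wording leaves three possibilities.
   - All men hold one, as Section 7.3.2 literally says. The interim dates and weights then separate intervention from control.
   - Both intervention arms hold one. Having the card then separates intervention from control.
   - Only incentive men hold one, if the sentence is confined to the section it stands in. Having the card then identifies SMS+I.

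   Allocation is disclosed, at least in part, under each.
4. **Do the stated safeguards prevent it?** An assessor new to the man, or unaware of his group beforehand, learns it from the card. A man who says nothing about his group still hands the card over if the Fieldworker is to complete it. No section withholds the card.
5. **When in the visit does it happen?** A measured weight can be entered only after the scale has been read. If the card first appears then, the reading has already been made blind. If it appears earlier, for example when the man arrives, the weighing is exposed too. In both cases whatever comes afterwards is exposed, including help with questionnaires (Section 6.6) and the adverse event questions asked at 12 months (Section 8.3).
6. **Is the order at 12 months fixed?** Section 6.2 puts weighing first for the 3-, 6- and 24-month visits. It allows the 12-month visit to be reduced to the same short weigh-in as a Covid-19 option, but states no order for the usual 30-minute 12-month visit.
7. **How many men could be affected?** With 195 per arm, at most 390/585, or two thirds, could bring a card with interim entries if both intervention arms hold one. The figure is 195/585, or one third, if only incentive men do. Both are ceilings, because the man must attend and bring the card, and no rate is given for that.
8. **Targets.** Sections 6.1 (item v) and 7.3.2 put target weights on the card without restricting this by arm. Section 7.2 sets none for controls. As written, these do not agree.

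**The case against.** The strongest reply is about timing and measurement. The entry follows the reading, so completing the card cannot alter a weight already taken. Calibrated scales, a common clothing request and the participant's signature leave little room for influence, and the signed hard copy is the source record (Section 10.1). Section 6.4 also says the blinding procedure was tested in the Feasibility Study and found workable. This stands as regards the likely effect on the weight. It does not remove the conflict between the two instructions, and it does not protect the rest of the visit.

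A second reply is that the phrase about all men in Section 7.3.2 is loose. The same section speaks of all participants being endowed with the incentive, which can only mean the incentive arm. That is a fair reading, but a card held by one arm alone still discloses that arm.

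A third reply is that card handling belongs in fieldworker instructions. That would answer an omission. Here the protocol states a rule that conflicts with its own design.

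A reader might go further and infer three things that the documents do not support:
- That the primary result is biased by some number of kilograms, or some share of the 3.3 kg planning difference. No passage gives a basis for any such shift.
- That controls receive weight targets, diluting both primary comparisons. Section 7.2 explicitly says none are set, so the other wording shows an inconsistency and not an exposure.
- That the 12-month questionnaires unblind the assessor before weighing, because the nested study adds a measure of the researcher relationship (Section 9.11). The protocol does not say where that measure sits or that it precedes the weighing.

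**Conclusion.** The point holds as a conflict between stated procedures. Followed as written, the card instruction discloses allocation to an assessor whom Section 6.4 requires to be blind, and no stated safeguard closes that route.

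The likely bias in the 12-month weight is small if the card is first seen after the reading. It is less certain if the card is seen before. This is a judgement from the order of events and the weighing procedure; the documents allow no calculation. The conclusion assumes that men bring the card and that the Fieldworker completes it as told. The card's layout is not shown, but the dates and weights that the text says it carries are enough. The change is worth making because it protects a property the protocol claims and needs only wording.

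**What to change.** 1. State in Sections 6.4 and 6.6 that at 12 months the weight is taken, entered on the CRF and signed before any questionnaire is started.
2. State in the same places that the 12-month assessor neither asks for, sees nor completes the appointment card, and except that visit from the instruction in Section 7.3.2. The man may write in his own 12-month weight. Intervention men also receive it through the automated message (Section 7.3.1).
3. Say which arms receive the card, and reconcile Sections 6.1 (item v) and 7.3.2 with Section 7.2 on whether a control's card shows a target.

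The cost is a change of wording in the protocol and the fieldworker instructions. It needs no extra visits, staff or data.
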